**Figure 2 F2:**
[figure not shown]
Flow diagram of recruited general practitioners.

From December 2004 GPs included in this study consecutively screen all eligible adults (aged 18 years or older) with symptoms (first experienced within the previous 28 days) of acute infection of the respiratory system. Inclusion criteria for patients are a consultation for common cold, pharyngitis, tonsillitis, rhinosinusitis, tracheo-bronchitis, otitis media, influenza, acute exacerbations of asthma or COPD, or community acquired pneumonia, the GPs intention to prescribe antibiotics on the basis of evidence-based guidelines, and written informed consent. Exclusion criteria for patients are antibiotic use in the previous 28 days, intravenous drug use, psychiatric disorders or inability to give written informed consent, not being fluent in German, severe immunosuppression (e.g. in HIV-infection, after solid organ transplantation or under chemotherapy), cystic fibrosis, active tuberculosis, and need for immediate hospitalisation. Study practices complete the trial after including 20 patients or at the anticipated end of the trial in December 2005.

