**Specialisation**		
General medicine – n (%)	25 (47)	188 (54)
Internal medicine – n (%)	26 (49)	148 (43)
Other – n (%)	2 (3.8)	9 (2.6)
**Years in private practice **– median [IQR]	15 [6.2 – 20]	16 [9.0 – 23]
**Years of postgraduate training **– median [IQR]	8.8 [7.7 – 9.7]	8.9 [7.6 – 11]
**Years since diploma **– median [IQR]	25 [15 – 29]	26 [14 – 31]

When a participating GP intends to give antibiotic treatment to an eligible patient based on clinical criteria and the patient gives written informed consent, the GP calls the study centre and the patient is randomly allocated to one treatment group or the other. The GP then takes a blood sample from the patient and sends it by courier service to the laboratory of clinical chemistry at the University Hospital Basel. This laboratory measures ProCT in all patients. Additionally, the GP documents patient baseline data on signs and symptoms, diagnostic procedures, diagnosis, co-morbidity and prescribed medication.

Where patients are randomised to the ProCT-arm, GPs will be informed about ProCT results and given recommendations about appropriate antibiotic therapy within 2–4 h after the blood is taken depending on the location of the practice. A cut-off ProCT level of 0.1 μg/l is used to rule out a bacterial respiratory tract infection. This value is identical to the cut-off used for the evaluation of patients in the emergency department of the University Hospital Basel [30]. In patients with a ProCT level below 0.1 μg/l, the diagnosis of a bacterial respiratory tract infection is considered highly unlikely, and the GP is encouraged to look for viral or alternative causes. Accordingly, the use of antibiotics is discouraged. In patients with a ProCT level above 0.25 μg/l, a bacterial respiratory tract infection is considered the most likely diagnosis and the use of antibiotics is recommended. For ProCT levels from 0.1 to 0.25 μg/l, a bacterial infection is unlikely and antibiotic treatment is not advocated.

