The GP then informs the patient about antibiotic treatment by phone. Patients in whom antibiotics are given will be asked to use a delayed prescription or to come back to the practice to pick up the antibiotic there. For patients in whom antibiotics are withheld based on ProCT levels of 0.25 μg/l or below, a follow-up measurement of ProCT within 24 hours is mandatory. If the ProCT level on this initial follow-up is >0.25 mg/l or if it has increased by more than 50% from its initial value without clinical improvement of the patient, the use of antibiotics is recommended.

In the ProCT group, all patients treated with antibiotics will be reassessed at Day 3. Discontinuation of antibiotic treatment is recommended if the ProCT level has decreased at least to 0.25 μg/l or below.

GPs draw blood samples and document therapy at each follow-up visit. They also collect information on days with restrictions and days off work at 1 week (6–8 days) after randomisation for all patients. Medical students, blinded to treatment allocation of patients and to the goal of the trial, will conduct standardised follow-up interviews at 14 and 28 days by phone. The patient flow will be monitored according to current guidelines and in agreement with the CONSORT statement [43]. We will use Teleform^® ^(Cardwell, Cardiff, GB) for data entry.

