### Outcomes and hypotheses

The primary outcome is days with restrictions from ARTI within 14 days after randomisation. Secondary outcomes are antibiotic use in terms of antibiotic prescription rate and duration of antibiotic treatment in days, days off work and days with side-effects from medication within 14 days, and relapse rate from ARTI within 28 days after randomisation.

Our hypothesis is that the clinical outcome for patients with ARTI will be no worse under ProCT-guided treatment, but patients with ProCT-guided treatment will have lower total antibiotic use; specifically a 20% lower antibiotic prescription rate and a 20% shorter antibiotic duration compared to patients treated under the standard approach.

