### Statistical analysis

With a non-inferiority trial, an intent-to-treat analysis is not necessarily conservative. For the primary outcome, we will need to provide several intent-to-treat analyses under different assumptions about patients who do not complete the trial, and a per-protocol analysis. Per-protocol analyses are planned for all secondary outcomes [44].

All outcomes will be analysed by a generalised linear model, assuming an appropriate distribution for each outcome and using the same set of covariates. These covariates will be: age, sex, education and a baseline score of the degree of restricted activity reported by the patient. 95% confidence intervals will be reported for the difference between treatment groups.

For the primary outcome, the assumed distribution will be normal; that is, analysis will be by multivariate linear regression. As a sensitivity analysis, the GP will be added to the model as a random effect and the model re-fit to the data from all GPs with only one GP per practice and with at least 10 patients per GP. Our experience from a previous trial (ISRCTN57824788) is that the difference between GPs has little influence on patient reported outcomes.

For secondary outcomes, assumed distributions will be binomial (i.e. for prescription of antibiotics) or normal (i.e. duration of antibiotic treatment). Duration of antibiotic treatment will be analysed only for those patients who receive antibiotics. We will also report a confidence interval for the difference in the antibiotic prescription rate between treatment groups. As a sensitivity analysis, we will repeat this calculation using a method appropriate for a cluster sample, where each GP forms a cluster and using only data from GPs with one GP per practice and with at least 10 patients per GP.

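### Antibiotic duration is compared only among recipients, a post-randomisation subset that the ProCT rule selects differently by arm, and no stated analysis directly estimates total antibiotic days

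*Protocol article*

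**What the plan says.** Under Outcomes and hypotheses, the protocol article expects that "patients with ProCT-guided treatment will have lower total antibiotic use", spelled out as "specifically a 20% lower antibiotic prescription rate and a 20% shorter antibiotic duration". Study aims also names reduced total antibiotic use as an objective.

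Under Statistical analysis, the rule for duration is: "Duration of antibiotic treatment will be analysed only for those patients who receive antibiotics". The model is normal, with age, sex, education and a baseline restriction score as covariates. The prescription rate is analysed separately, with a confidence interval for the difference between groups. Per-protocol analyses are planned for all secondary outcomes.

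Three other places bear on who counts as a recipient:

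- **Participants:** an inclusion criterion is "the GPs intention to prescribe antibiotics on the basis of evidence-based guidelines".
- **Data collection and management, starting treatment:** in the ProCT arm below 0.1 μg/l, "Accordingly, the use of antibiotics is discouraged". From 0.1 to 0.25 μg/l treatment is not advocated; above 0.25 μg/l it is recommended.
- **Data collection and management, stopping treatment:** in the ProCT arm, treated patients are reassessed at Day 3, and "Discontinuation of antibiotic treatment is recommended if the ProCT level has decreased" to 0.25 μg/l or below.

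The same section says of the assay: "This laboratory measures ProCT in all patients".

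**The concern.** Whether a patient receives antibiotics is decided after allocation, and the intervention is designed to change it. Controls enter because the GP means to treat them, so nearly all should be recipients. In the ProCT arm, recipients should be weighted towards higher ProCT, which the protocol reads as more likely bacterial infection. The two recipient groups can therefore differ in case mix even if ProCT guidance does nothing to course length. The selecting variable is not in the model, and the listed covariates cannot be relied on to replace it. A per-protocol set does not restore the randomised comparison either.

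A patient spared antibiotics altogether is the effect the trial seeks, yet contributes nothing to the duration analysis. At stake is the reading of an explicit secondary hypothesis: the duration contrast may be diluted or distorted, while total exposure, the quantity in the aim, has no stated estimate or interval.

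**Working it through.** **The plan's own figure.** The only sample size given is for the primary outcome. With margin 1 day, SD 4, one-sided 5% and 90% power, n = 2 × 4² × (1.645 + 1.282)² / 1² ≈ 274.1, so 275 per group. Then 275 / 0.90 = 305.6, so 306 per group and 612 in total. These reproduce and do not depend on the duration analysis.

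**Inputs for the duration check.**

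- From the article: the 20% lower prescription rate, the 20% shorter duration, the Day 3 recommendation, and the 24-hour ProCT half-life in successfully treated infection (Background).
- Assumed, because the article does not give them: all controls treated; the share *h* of patients with high ProCT; usual courses of 9 v 7 or 8 v 6 days for high v low ProCT.

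**Formulas.**

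- Control mean = *h*·d_high + (1 − *h*)·d_low.
- ProCT recipients' mean = antibiotic days in treated ProCT-arm patients / number treated.
- ProCT mean over all randomised = treated share × recipients' mean.

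**Results.** The "no effect" columns assume that ProCT does not change course length. The shortening column multiplies the ProCT recipients' mean by 0.8.

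| ProCT arm treated | Courses, high/low (days) | Control mean | ProCT recipients' mean | Recipients only, no effect | Recipients only, true 20% shortening | All randomised, no effect |
|---|---|---|---|---|---|---|
| 80% (25% high + 55% low) | 9/7 | 7.5 | 6.1/0.8 = 7.63 | +1.7% | −18.7% | 6.1 v 7.5, −18.7% |
| 80% (all high) | 9/7 | 8.6 | 9.0 | +4.7% | −16.3% | 7.2 v 8.6, −16.3% |
| 80% (all high) | 8/6 | 7.6 | 8.0 | +5.3% | −15.8% | 6.4 v 7.6, −15.8% |
| 50% (all high) | 8/6 | 7.0 | 8.0 | +14.3% | −8.6% | 4.0 v 7.0, −42.9% |
| 25% (all high) | 9/7 | 7.5 | 9.0 | +20% | −4% | 2.25 v 7.5, −70% |
| 25% (all high) | 8/6 | 6.5 | 8.0 | +23.1% | −1.5% | 2.0 v 6.5, −69.2% |

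In the 80% rows the last two columns agree only because the treated share and the shortening factor are both 0.8.

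**Simulation.** With 275 per arm, courses of 8 v 6 days, SD 3 (assumed) and no effect on course length, the recipients-only test found a significantly longer duration under ProCT in 29%, 86% and 96% of trials at treated shares of 80%, 50% and 25%. The all-randomised comparison found significantly fewer antibiotic days in 98-100%.

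**Effect of the Day 3 recommendation.** Take the 25%, 9/7 row. If a share *s* of ProCT recipients stops at day 3, their mean is 9(1 − *s*) + 3*s* = 9 − 6*s*. It equals the control mean of 7.5 at *s* = 25%, and at *s* = 50% it is 6.0 v 7.5, or −20%. Three half-lives take a starting value of 0.25 × 8 = 2.0 μg/l down to 0.25 μg/l, so many recipients could qualify if the infection responds.

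**Reversal despite a true 20% shortening.** This needs a wider course-length gap and a low treated share. At 25% treated, 10 v 5 days gives 8.0 v 6.25 (+28%) and 9 v 6 days gives 7.2 v 6.75 (+7%).

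**Both stated reductions together.** 1 − 0.8 × 0.8 = 0.36, or 36% fewer days per randomised patient.

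**The case against.** The strongest reply is that the distortion is small at the protocol's own planning figure. With a 20% lower prescription rate, spurious lengthening is about 2-5%, and a true 20% shortening still shows as roughly 16-19%. This stands. A reader might infer that the plan will show about 20% longer courses under ProCT. That figure needs only about a quarter of the ProCT arm to be treated and no effect on course length, and the second condition sets aside the Day 3 recommendation. The documents do not support it as the expected result. They do not exclude it either, since the treatment rule could cut prescriptions by more than 20%.

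A reader might also infer that the ProCT arm would have few recipients. At the hypothesised rate, about 0.8 × 275 = 220 of 275 would be treated.

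A second reply is that total use is covered by its two components. The rate is compared between groups with an interval, and mean total days equals rate times mean duration among recipients when both come from the same patients. So it would be too strong to say that the plan leaves total use unaddressed. What remains is that no combined estimate, interval or test is stated, and that one of the two components lacks the protection of randomisation.

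Third, duration is one secondary outcome. If high-ProCT patients do have longer courses, the bias runs against ProCT and does not create a benefit. That limits the severity, but does not make the comparison valid.

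**Conclusion.** The point holds in a limited form. The recipients-only duration comparison is open to selection bias under any of these inputs, because receipt is a consequence of allocation and the selecting variable is outside the model. No stated analysis directly estimates or tests lower total antibiotic use.

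The size is an assumption. It rests on all controls being treated, courses about 2 days longer at high ProCT, and no effect of ProCT on course length. On that footing, spurious lengthening is about 2-5% with 80% of the ProCT arm treated and about 20-23% with 25% treated. A reversed sign is possible but not expected. This should be fixed, but it concerns a secondary outcome; the primary outcome and sample size are untouched.

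**What to change.** Add antibiotic days per randomised patient as the main analysis of total antibiotic use. Include all patients as randomised, count zero days for those known not to have been treated, and report the difference in means with a robust or bootstrap 95% confidence interval. Patients lost to follow-up are missing, not zero.

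Do not apply the 20% duration target to this quantity. A 20% fall in prescriptions alone would meet it with no shortening of courses, while the two stated reductions together imply about 36% fewer days.

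Keep duration among recipients, labelled as a descriptive, non-randomised comparison. It can be shown by baseline ProCT level, since ProCT is measured in both arms.

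The cost is a change of analysis wording: no new data and no change in sample size. The drawback is that many zeros rule out relying on the plain normal model, hence the robust or bootstrap interval. Recruitment stood at 213 patients (35% of target) in April 2005, so the change can be made before analysis.

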### Time plan for the study

Patient recruitment began in December 2004 and is planned to continue until December 2005. By April 2005, 213 patients (35% of target) have been recruited into the trial.

## Discussion

The present trial is the first randomised controlled trial to evaluate whether ProCT testing in a primary care setting reduces antibiotic use for ARTI without compromising patient relevant outcomes. In case of success, implementing this new approach into daily practice could largely improve the management of ARTI in primary care by avoiding unnecessary antibiotic use and preventing antibiotic resistance.

Our trial may have some limitations. First, this is an open intervention trial, and GPs may learn from their experience with ProCT testing and improve their clinical judgement. We cannot control for this bias, but at least this bias will be conservative for outcomes such as the antibiotic prescription rate and the duration of antibiotic therapy. Second, we expect to have recruited highly motivated primary care physicians, interested in the research question and able to provide high quality data. Motivated, interested GPs might be more reluctant to prescribe antibiotics for ARTI; thus they might consider patients for antibiotic treatment which are on average sicker than patients considered by disinterested GPs. However, we believe that ProCT-guided ARTI management will lead to a reduced antibiotic use even in such a setting of motivated GPs and the potential bias will be conservative. Third, while measurement of ProCT at a central laboratory is not ideal for routine primary care, there are still a considerable number of general practices that send blood samples daily to a laboratory for analysis of C-reactive protein or leucocytes. Therefore this should also be feasible for ProCT until a near-patient test, which is currently being developed, becomes widely available.

## Abbreviations

ARTI, acute respiratory tract infections

GP, general practitioner

ProCT, procalcitonin
